## Methods and analysis

### Study setting

Study flow, study settings and other information are presented in figure 1 and table 1. The study recruitment target is 400 participants who start ADT as primary management of de novo metastatic PCa or as secondary management for PCa recurrence after localise treatment. Participants can be high-risk M0 or M1 stage, main inclusion criterion is that long-term ADT treatment is started. These men will be randomised 1:1 (200+200) to receive either 80 mg of atorvastatin daily or placebo until disease recurrence that is, development of castration resistance, death or maximum of ten years. Sample size is based on a power calculation from a previous retrospective study.^23^

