### Study endpoints

Primary endpoint is the time to disease progression after starting ADT/antiandrogen therapy. Secondary endpoints are (1) PCa-specific mortality and overall survival, (2) change in serum cholesterol during the intervention and its role in predicting time to disease recurrence in the placebo arm, (3) occurrence of adverse tumour traits predicting development of castration resistance in circulating cell free DNA, (4) changes in fasting blood glucose during ADT, (5) occurrence of cardiovascular events during ADT and (6) Quality of life (QoL) during ADT.

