### Study flow

Study flow and schedule is presented in figure 1 and table 2. Patients are recruited at urology outpatient clinic at urologists’ visits. If the inclusion criteria are met and the exclusion criteria are not and the participant signs informed consent form, he is given a study number (ranging between E-001 to E-400) and he receives either 80 mg atorvastatin or placebo according to the study arm randomly allocated for the study number. No blocking or other restrictions will be implemented for randomisation. Only the national study coordinator in each country will be able to see which study arm the participant has been randomised to. The participant will then receive first dose of the respective study drug randomised to his study number. The drug boxes and capsules containing atorvastatin and placebo will be identical in appearance. All researchers, nurses and study participants will remain blinded to the allocation sequence until termination of the study and closure of the study data.

**Table 2 T2:** Study flow and timing of the laboratory and blood sample collection

	Enrolment	Allocation	Follow-up‡			
Timepoint		0	6 months	12 months	18 months	24 months
Enrolment:						
Eligibility screen	x					
Informed consent	x					
Allocation		x				
Interventions:*						
Atorvastatin			x	x	x	x
Placebo			x	x	x	x
Assesments:						
Serum PSA (ng/mL)	x		x	x	x	x
Alkaline phosphatase (U/L)	x		x	x	x	x
Creatinine (µmol/L)	x		x	x	x	x
Serum creatine kinase (U/L)	x		x	x	x	x
Alanine aminotranspherase (U/L)	x		x	x	x	x
Fasting blood glucose (mmol/L)	x		x	x	x	x
Lipid levels (total cholesterol, LDL, HDL and triglycerides) (mmol/L)	x		x	x	x	x
Cell free DNA (subgroup)†	x					
QoL	x			x		x

*Allocation 1:1 to have eighter 80 mg atorvastatin or placebo daily

†Cell free DNA is measured before allocation and after occurrence of castration resistance.

‡Follow-up until disease recurrance, death or max. 10 years

HDL, high-density lipoprotein; LDL, low-density lipoprotein; PSA, prostate-specific antigen; QoL, quality of life.

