Control visits are scheduled at 6-month intervals to suit common clinical practice. Control visits are done by a clinician, complemented with measurements done by a research nurse. For each control visit the participant returns remaining capsules from the previously delivered ration and will receive a new one according to his study number. Number of the remaining capsules will be counted and saved in the REDCap, trial database, to monitor compliance. In every visit, serum PSA (ng/mL), lipid levels (total cholesterol, high-density lipoprotein (HDL), low-density lipoprotein (LDL) and triglycerides, mmol/L), alkaline phosphatase (U/L), creatinine (μmol/L), and fasting glucose (mmol/L) will be measured (table 2) and the participant is asked about symptoms that are suggestive of metastases and about possible adverse effects of the study drug. Serum creatine kinase (U/L) and alanine aminotransferase (U/L) is also measured at each visit.

Blood samples are taken and stored at 6-month intervals to monitor changes in tumour markers and occurrence of adverse tumour characteristics after initiation of ADT. QoL during the intervention will be charted once a year using validated WHOQOL-BREF QoL questionnaire.^33^

Follow-up is continued until development of castration resistance, drop out from the study, death or maximum of 10 years. Participants developing castration resistance are given an opportunity to carry on with their assigned treatment as statins have been linked to longer cancer-specific survival. Unblinding will be performed after recruitment target has been reached and all participants have been followed for minimum of 12 months.

PCa treatment apart from the study drug will be up to the discretion of the attending clinician. All laboratory results, symptoms and possible imaging results will be recorded in the REDCap database. All clinical decisions regarding early chemotherapy and imaging will be made on the discretion of the clinician and recorded in the REDCap database.

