### Sample size calculation

In a cohort study by Harshman *et al*,^23^ among men starting ADT, 58% of the statin users and 75% of non-users of statins progress to castration resistance during median 5.8 years. We used these crude percentages for sample size calculations.

With alpha and beta values of 0.05 and 0.20 (power=0.80), sample size of 400 men will be enough to detect a risk difference with HR 0.65 (figure 2). We assume 10% drop-out rate in each study arm. The programme ‘PS—Power and sample size, V.3.1.2’ was used for the calculation.

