### Statistical methods

Distribution balance of PCa clinical characteristics such as TNM stage at diagnosis, Gleason score and PSA at time of diagnosis will be presented in a patient characteristics table, stratified by study arms. Categorical variables are displayed as absolute count frequencies and relative frequencies, that is, proportion within study arm. Continuous variables are presented as median and IQR. Minimum and maximum values are not shown to ensure anonymity of the participants.

Recurrence-free survival, that is, time from ADT initiation to castration resistance, will be analysed by using Kaplan-Meier (KM) estimator, stratified by study arm. The statistical significance of the difference between the survival estimates is tested with log-rank test. No adjustments will be used for KM estimator as the study intervention is randomised. Risk of death, as well as risk for occurrence of adverse tumour traits among men receiving atorvastatin compared with men receiving placebo will be estimated using Cox proportional hazards regression.

Univariate analysis of changes in serum lipid levels is performed by calculating the difference after—before for each participant. The statistical significance of the difference between the study arms is analysed by Mann-Whitney U test (or by t-test if under normality). These results are complemented with boxplots. Multivariable analysis for difference in serum lipid levels between the study arms are performed by fitting a logistic regression model such that the study arm is used as the response variable whereas lipid level differences are used as predictors (ie, each lipid level difference as an independent predictor). Lipid levels are expected to display heavy multicollinearity; therefore, variance inflation factors (VIF) are calculated for each coefficient afterwards, and possible adjustments made by dropping predictors with extreme VIFs (>10).

The occurrence of adverse tumour genomic traits will be analysed by calculating the proportion of participants developing adverse tumour genomic traits. The statistical significance between the proportions is tested by proportions test.

The WHOQOL-BREF patient-reported outcome (PRO) of the quality-of-life is analysed by tabulating absolute and relative frequencies. χ^2^ test for homogeneity is used to test the statistical significance of the difference between the study arms of each PRO item.

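### Quality of life is compared item by item with an unordered chi-square test that leaves answer order and the baseline questionnaire unused: valid per item, but inefficient, without an effect size, and with no stated main score or multiplicity rule

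*Protocol article*

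**What the plan says.** The Study endpoints section of the protocol article lists "Quality of life (QoL) during ADT" as the last of six secondary endpoints and names no score. Under Study flow, "QoL during the intervention will be charted once a year using validated WHOQOL-BREF QoL questionnaire". Table 2 marks the questionnaire at enrolment, 12 months and 24 months, so a baseline answer will exist.

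The Statistical methods section gives the analysis in two sentences. The "patient-reported outcome (PRO) of the quality-of-life is analysed by tabulating absolute and relative frequencies", and a chi-square "test for homogeneity is used to test the statistical significance of the difference between the study arms of each PRO item". The section names no domain or total score, main item, time point, use of the enrolment answers or multiplicity rule for this endpoint.

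The same section treats another before-and-after outcome differently. For serum lipids it takes each man's change and compares the arms with a Mann-Whitney test or a t-test.

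A detailed SAP is promised before the final analysis; it is not shown.

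**The concern.** A homogeneity test treats answer categories as nominal. Shuffle the categories and the p value is unchanged, so a small p value does not say whether quality of life was better or worse on atorvastatin. The test also spreads its power over every way in which two distributions can differ, when the question is whether answers shift up or down. The enrolment questionnaire, which would remove part of the between-person variation, plays no part in the comparison as described.

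A second, separate matter is the number of tests. One p value per item, with no main score and no correction stated, invites reading meaning into an isolated item.

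At stake is whether the trial can give a usable answer on quality of life: one difference with an interval, estimated with the precision that the collected data allow.

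**Working it through.** The article gives no power, effect size or item count for quality of life, so there is no figure of its own to reproduce.

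**Inputs from the article**
- Allocation is 1:1 with 200 per arm (Study setting), and "We assume 10% drop-out rate in each study arm" (Sample size calculation). So 200 × 0.90 = 180 per arm at most.
- Alpha of 0.05 is stated for the primary endpoint: "With alpha and beta values of 0.05 and 0.20 (power=0.80), sample size of 400 men will be enough to detect" (Sample size calculation). Its use for each item is an assumption.

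**Assumed inputs (not in the article)**
- Five ordered answers with control proportions of 5, 15, 30, 35 and 15%.
- A shift of 0.2, 0.3 or 0.4 SD on an underlying normal scale.
- A correlation with baseline of 0.5, with 0.7 as a variant.
- 10 to 30 items.

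**Step 1: validity.** With no shift, the simulated chi-square test rejects in about 5% of runs (4.7–5.2% at 180 per arm). Ignoring order and baseline does not inflate the error rate.

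**Step 2: power of the chi-square test, by formula.** With control proportions p and shifted proportions q, the non-centrality is λ = n × Σ(p − q)²/(p + q). The test has 4 df and a critical value of 9.49. A 0.3 SD shift turns the proportions into 2.6, 10.1, 25.5, 38.7 and 23.1%.
- 0.2 SD: λ = 180 × 0.01794 = 3.23, power 26%.
- 0.3 SD: λ = 180 × 0.03986 = 7.17, power 55%.
- 0.4 SD: λ = 180 × 0.06967 = 12.54, power 82%.

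**Step 3: comparison by simulation.** The adjusted analysis is a linear model of the item on arm and the baseline item. Ranges span separate simulation runs.

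| Per arm | Shift (SD) | Chi-square | Mann-Whitney | Adjusted, r = 0.5 | Adjusted, r = 0.7 |
|---|---|---|---|---|---|
| 180 | 0.2 | 26–27% | 43% | 52–53% | 64% |
| 180 | 0.3 | 55–56% | 76% | 85% | 94% |
| 180 | 0.4 | 83–84% | 94–95% | 98% | 99.7% |
| 90 | 0.3 | 27–28% | 47% | 55–57% | 70% |

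At 180 per arm and 0.3 SD, using the order of the answers gains about 20 points and using the baseline about another 9 (r = 0.5). The table compares methods on a single item; it does not model a domain score.

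**Step 4: why 90 per arm is a fair scenario.** Study flow ends follow-up at castration resistance. The article takes median times to progression of 12–15 months (de novo metastatic) and 33 months (recurrent). Assume exponential times and no questionnaire after progression. The number left of 200 at month t is then 200 × 0.5^(t/median), before drop-out.
- 12 months: 200 × 0.5^(12/12) = 100 to 200 × 0.5^(12/33) = 155.
- 24 months: 200 × 0.5^(24/12) = 50 to 200 × 0.5^(24/33) = 121.

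**Step 5: chance findings at one time point.** With k independent items the chance of at least one is 1 − 0.95^k, and the expected number is 0.05k.

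| Items | At least one | Expected number |
|---|---|---|
| 10 | 40% | 0.5 |
| 20 | 64% | 1.0 |
| 26 | 74% | 1.3 |
| 30 | 79% | 1.5 |

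Correlation changes this little: for 26 items, simulation gives 70% at a correlation of 0.3 and 69% at 0.5. Four scores without correction give 1 − 0.95^4 = 18.5%.

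**The case against.** The strongest reply is that randomisation makes each unadjusted comparison valid, that the article summarises the endpoint in two sentences, and that domain scoring, the main time point, multiplicity and interval reporting commonly belong in the SAP. Much of this stands. Silence on those items is not in itself a fault, and the SAP could add a multiplicity rule. What it does not answer is that the article names a particular test at the item level. Better use of the data means replacing that test, not merely adding detail to it.

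Four stronger readings are tempting and are not supported.
- *Ignoring order and baseline causes false positives.* It does not: the error rate per item stays near 5%. Chance findings come from the number of items.
- *Every item is tested at every visit.* The Statistical methods section names no time point, and Table 2 ("Study flow and timing of the laboratory and blood sample collection") is a collection schedule. Multiplying the item count by the number of visits therefore has no basis in the text.
- *Scattered significant items are certain.* Even with 26 independent items there is a 26% chance of none.
- *A consistent shift would be missed.* If 26 items each shifted by 0.3 SD at 180 per arm, about 26 × 0.55 = 14 would be expected to reach significance, against 1.3 by chance. The power loss matters most for small shifts, shifts confined to a few items, and later visits with fewer men.

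**Conclusion.** The point holds as one of efficiency and interpretability, with multiplicity as a separate and lesser matter. The stated test is valid but inferior to what the collected data allow. At 180 per arm it loses about 14 to 30 points of power per item against a baseline-adjusted comparison for shifts of 0.2 to 0.4 SD (r = 0.5), and it yields no direction or effect size. Whether its power is low in absolute terms depends on the shift: at 0.4 SD it still exceeds 80%. With the item tests uncorrected, at least one chance finding at a single time point is likely (40–79% for 10–30 independent items, about 70% for 26 correlated items).

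These figures rest on the assumed answer distribution, item count, baseline correlation and 0.05 level per item. The ordering of the answers is itself an assumption about the instrument. The endpoint is secondary and the primary conclusion is unaffected, so this is a change that should be made, not one on which the trial depends.

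**What to change.** In the forthcoming SAP:
- Replace the item-level tests with pre-specified domain scores, or one main score, at a named time point.
- Compare the arms by ANCOVA, or by a repeated-measures model, adjusted for the baseline score. Report the difference with its 95% CI.
- Control multiplicity across scores, for example by Holm or Bonferroni, or by naming one main score. Four uncorrected scores would still carry an 18.5% chance of at least one false positive.
- Keep the item frequencies as descriptive tables without p values.

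The cost is SAP wording: the enrolment questionnaire is already scheduled, so no new data are needed. There are two small downsides. Item-level p values are given up. A repeated-measures model needs a missing-at-random assumption, which deserves a sentence of justification because follow-up may stop at progression.

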**Methods and analysis:**

In this randomised placebo-controlled trial, a total of 400 men with de novo metastatic prostate cancer or recurrent disease after primary treatment and starting ADT will be recruited and randomised 1:1 to use daily 80 mg of atorvastatin or placebo. All researchers, study nurses and patients will be blinded throughout the trial. Patients are followed until disease recurrence or death. Primary outcome is time to formation of CR after initiation of ADT. Serum lipid levels (total cholesterol, high-density lipoprotein (HDL), low-density lipoprotein (LDL) and trigyserides) are analysed to test whether changes in serum cholesterol parameters during ADT predict length of treatment response. Furthermore, the trial will compare quality of life, cardiovascular morbidity, changes in blood glucose and circulating cell-free DNA, and urine lipidome during trial.

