Study type	Interventional, allocation: randomised, Intervention model: parallel assignment with 1:1 allocation ratio, Masking: double blind (subject, caregiver, investigator, outcomes assessor), Primary purpose: prevention, phase III
Date of first enrolment	July 2019
Target sample size	400
Recruitment status	Recruiting
Primary outcome(s)	Castration resistance
Key secondary outcomes	Lipid levels, Prostate cancer mortality and overall survival, Circulating cell free DNA, Fasting blood glucose, Occurrence of cardiovascular events during ADT, Quality of life

ADT, androgen deprivation therapy.

The study will be carried out in collaboration between urological departments of University Hospitals and central hospitals in Finland, the Herlev University Hospital in Denmark, the Tartu University Hospital in Estonia and Vestfold Hospital Trust in Norway (table 1).

Study data are collected and managed using REDCap electronic data capture tools hosted at Tampere University.^31 32^ Only the primary investigators, study nurses and registered study coinvestigator from each participating site will have access to the platform. All laboratory results, symptoms and results from imaging studies done at the discretion of the attending clinicians are recorded in the database. All clinical decisions besides the study drug, for example, use of early chemotherapy, abiraterone or other drugs in adjunct with ADT will be up to the discretion of the attending clinician and allowed but will also be recorded in the REDCap database.

Follow-up is continued until development of castration resistance, death or maximum of 10 years. Participants are given the opportunity to carry on with the intervention even after development of castration resistance to observe effects on survival. Unblinding will be performed after recruitment target has been reached and all participants have been followed for minimum of 12 months.

Castration resistance is defined as either PSA progression (three consecutive rises of PSA measured at least 1 week apart with two >50% increases over the nadir and PSA >2 ng/mL) or radiological progression (appearance of two or more lesions in bone scan or soft tissue enlargement as per RECIST criteria) while serum testosterone is at the castrate level (<50 ng/mL or 1.7 nmol/L).

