### Inclusion and exclusion criteria

Inclusion criteria for participants are histopathologically confirmed metastatic adenocarcinoma of the prostate or high-risk M0 stage recurrent PCa for which androgen deprivation or antiandrogen therapy is initiated no longer than 3 months before recruitment, willingness to participate and signing of informed consent (figure 1).

Exclusion criteria for participants are regular statin use at the time of recruitment or within 6 months of it, previous adverse effects during statin therapy, familial hypercholesterolaemia or very high total cholesterol (9.3 mmol/L or above), clinically significant renal (serum creatinine above 170 µmol/L) or liver insufficiency (serum alanine aminotransferase more than two times above the upper limit of normal range), and use of drugs that may interact with statins (St John’s Wort, HIV protease inhibitors, ciclosporin, macrolide antibiotics, fucidic acid, phenytoin, carbamazepine, dronedarone or oral antifungal medication) (figure 1).

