Subgroup analyses will be performed stratified by type of ADT or antiandrogen therapy initially selected; GnRH agonists/antagonists, antiandrogen, orchiectomy or other. Men who start with antiandrogen therapy often change to GnRH agonists/antagonists or orchiectomy when PSA increases during ADT. This is allowed and PSA recurrence during antiandrogen therapy is not considered as disease progression as serum testosterone needs to be at castrate level as well for meeting the primary endpoint.

Another subgroup analysis will be stratified by whether or not the participants have received local therapy (radiation or surgery) for PCa in addition to ADT and by type of additional therapy participant has received; docetaxel, abiraterone, enzalutamide or apalutamide at hormone-sensitive stage in addition to ADT.

All analyses will include only participants with available data, imputations will not be used. Detailed statistical analysis plan is published before final data analysis. All analyses are performed using SPSS V.27, Stata V.17 and R V.4 statistical softwares.

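### The additional-therapy subgroup has no cut-off at randomisation, so membership can depend on study arm and the subgroup comparison can show spurious effect modification

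*Protocol article*

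**What the plan says.** Three subgroup variables appear in the Protocol article under Statistical methods.

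- Type of ADT, which has a time anchor: "stratified by type of ADT or antiandrogen therapy initially selected".
- Local therapy, which has none: "stratified by whether or not the participants have received local therapy (radiation or surgery) for PCa in addition to ADT".
- Additional systemic therapy, whose only time limit is the hormone-sensitive stage: "by type of additional therapy participant has received; docetaxel, abiraterone, enzalutamide or apalutamide at hormone-sensitive stage in addition to ADT".

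The choice of additional therapy is not part of the trial design. Study setting states that "use of early chemotherapy, abiraterone or other drugs in adjunct with ADT will be up to the discretion of the attending clinician", and Study flow repeats this after describing the 6-monthly visits: "All clinical decisions regarding early chemotherapy and imaging will be made on the discretion of the clinician and recorded in the REDCap database". Additional therapy is not a stratification factor: "No blocking or other restrictions will be implemented for randomisation".

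Two further statements fix the window. Men may enter some time after ADT has begun, since "androgen deprivation or antiandrogen therapy is initiated no longer than 3 months before recruitment". The hormone-sensitive stage closes with the event that the trial counts: "Primary outcome is time to formation of CR after initiation of ADT".

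**The concern.** A subgroup supports a randomised comparison of arms only if membership is settled before treatment can influence it. Here a man can join the receiver group at any time up to the primary event.

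If atorvastatin does what the trial hypothesises, arm can affect membership in two ways. PSA course may prompt the clinician to add a drug, and a longer hormone-sensitive period gives more opportunity to receive one. Blinding prevents deliberate differences between arms but blocks neither route.

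At stake is the reading of effect modification. Many readers will ask whether atorvastatin adds anything on top of docetaxel or a newer hormonal agent. A subgroup defined in this way could suggest that its effect differs between receivers and non-receivers when it is the same in both.

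**Working it through.** **1. The wording.** The ADT-type subgroup is fixed by the initial choice. The same section explains that men on antiandrogens often change therapy when PSA increases, and that such a rise is not progression unless testosterone is at castrate level. PSA-driven treatment change is thus recognised and dealt with for one subgroup but not for the next. The castration-resistance definition under Study setting requires three consecutive PSA rises. This leaves an interval in which a rise could prompt added therapy before the endpoint is met.

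**2. Figures in the plan.** The article gives no uptake, timing or power for this subgroup, so there is no figure to reproduce. The inputs taken from it are 400 men randomised 1:1, HR 0.65, alpha 0.05 (sidedness not stated; two-sided assumed) and progression proportions of 58% and 75%, mean (0.58 + 0.75)/2 = 0.665.

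**3. Simulation.** All of the following are assumptions: control median 20 months at average prognosis; log-normal prognosis with SD 0.7; uniform censoring at 12 to 60 months; no effect of the added drug itself; one true HR of 0.65 for every man. A Cox model for arm was fitted within receivers and non-receivers. HRs come from 400,000 men. Rejection rates come from 2,000 trials of 400 men, using z = (b1 − b2)/√(s1² + s2²) at 1.96.

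| How membership arises | Received, atorvastatin / placebo | HR, receivers | HR, non-receivers | False interaction |
|---|---|---|---|---|
| Fixed at baseline, by prognosis only | 38% / 38% | 0.705 | 0.686 | 5.1% |
| Started in first 3 months regardless of arm | 38% / 38% | 0.690 | 0.693 | 5.3% |
| Constant start rate while hormone-sensitive | 50% / 44% | 0.689 | 0.742 | 5.6% |
| Triggered by a rise before progression | 33% / 39% | 0.828 | 0.649 | 14.4% |
| Receipt depends directly on arm and prognosis | 34% / 46% | 0.747 | 0.725 | 4.9% |

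The first row is the right yardstick, not 0.65. Varying prognosis alone pulls the marginal HR to about 0.70 overall and leaves a small gap between strata even when they are fixed at baseline. The Monte Carlo error of a 5% rate is √(0.05 × 0.95/2000) = 0.5 percentage points, so only the rise-triggered rule clearly exceeds nominal.

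**4. No true effect.** With a true HR of 1.0, the first four rules gave HRs between 0.99 and 1.01 and rejection rates of 4.6% to 5.4%. The last rule, where arm acts directly on receipt, gave 1.08 and 1.06. Both strata were shifted, with no false interaction (4.9%). Distortion therefore requires that arm influences membership.

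**5. A milder case at the planned size.** Suppose therapy is given at 6 months, more often to poor responders, to 18–19% on atorvastatin and 27–28% on placebo. Simulated HRs were 0.74 in receivers against 0.67 in non-receivers (frailty SD 0.5), or 0.81 against 0.71 (SD 0.8).

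- Receivers: 0.23 × 400 = 92 men, 92 × 0.665 = 61 events. Non-receivers: 308 × 0.665 = 205 events.
- SE of the difference in log HR: √(4/61 + 4/205) = 0.29.
- Gaps: ln(0.74/0.67) = 0.10 and ln(0.81/0.71) = 0.13, which are 0.34 and 0.45 SE.
- False interaction rate, Φ(−1.96 + δ) + Φ(−1.96 − δ): about 6% and 7%.

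Part of these gaps is the prognosis effect noted in step 3, because no baseline-defined comparator was run for this case.

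**The case against.** The strongest reply is that the article does not say that the therapy follows randomisation. ADT may have started up to 3 months before recruitment, and Study setting speaks of early chemotherapy and drugs given in adjunct with ADT. Many men may already be on the drug, or have it chosen, at entry. This stands: a reader might infer that the whole subgroup is defined after randomisation, and the text does not support that. What it supports is a definition that mixes the two.

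Second, a detailed analysis plan is promised before the final analysis and could supply the cut-off. It could, but the rule in print is more than silent. It sets a window that runs to the primary event, beside a subgroup that is anchored, and a plan that follows the wording inherits the problem.

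Third, the likely distortion is modest. This also stands. In the milder case the gaps are under half a standard error, and in all the simulated cases with a true HR of 0.65 both subgroup HRs stay below 1. A conclusion that atorvastatin works only with, or only without, a given drug is therefore not what these figures predict.

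Fourth, local therapy is a weaker example. Recurrent men start ADT after earlier local treatment, so for them this variable is largely settled before entry. The missing anchor matters only where local therapy could be given later.

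A reader might also suspect guaranteed event-free time from comparing receivers with non-receivers. The article plans analyses stratified by therapy, not that contrast, so the point does not apply.

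**Conclusion.** The concern holds as a defect in how the subgroup is defined. The stated rule lets membership be settled after randomisation and up to the primary endpoint, so study arm can influence it and the comparisons within subgroups lose the protection of randomisation.

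It does not follow that the subgroup results will be biased. Under assumed inputs the effect runs from none, when therapy starts early regardless of arm, to HR 0.83 against 0.65 with a 14% false interaction rate, when a rise before progression triggers therapy. A baseline definition gave 0.71 against 0.69 and 5.1%. Which case is nearest depends on when and why clinicians add therapy, and the article does not report this.

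The primary intention-to-treat log-rank comparison and the sample size are untouched. The definition should be corrected before unblinding, but it does not threaten the main conclusion.

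**What to change.** Define the additional-therapy subgroup by therapy started at or before randomisation, or documented by then as planned if that is recorded. Apply the same cut-off to local therapy where it could be given after entry. Report the arm-by-subgroup interaction alongside the subgroup HRs. Describe therapy added later only as a time-varying variable, in an analysis labelled descriptive.

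This changes analysis wording only and leaves treatment and recruitment as they are. There are two costs. Men whose treatment is intensified later count in the stratum not receiving therapy at baseline, so that stratum is less pure. And although the article says that therapy is recorded in REDCap, it mentions neither start dates nor therapy planned at entry. Their availability must be confirmed, and missing dates retrieved before unblinding.
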